### Objectives

The objectives of this study are to (1) assess the acceptability and feasibility of implementing the PEP across three urban clinical sites; (2) determine if a PEP will change patient preference for control in medical decision making, improve patient self-efficacy in patient-HCP communication, and increase patient activation; (3) determine if participation in the PEP is associated with an increase in diabetes self-management behaviors; and (4) explore the effect of the PEP on hemoglobin A
_1c_(HbA
_1c_) level.

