### Sample Size

Prior studies have pilot-tested interventions to increase patient activation and found that PAM scores increased by a range of 4-8 points [
30,
31]. This difference was statistically significant, is thought to be clinically significant, and translates to a moderate effect size, Cohen’s
*d*=0.48. Given the repeated-measures design of the study, setting alpha = .05 and beta = .2, and using the effect size calculated from the literature, the required sample size will be n=36 patients. It is our goal to have 40 participants complete the PEP intervention.

In anticipation of significant participant dropout over the course of the study, we aimed to enroll 40 patients from Bellevue Hospital Center, 20 from Gouverneur Health, and 20 from Woodhull Medical Center. From these patients, it was our goal that 20 from Bellevue Hospital Center and 10 each from Gouverneur Health and Woodhull Medical Center would complete the PEP intervention. Because of these concerns about dropout, all participants who were randomized to the immediate intervention group but unable to attend the PEP intervention at that time were contacted for the T1 assessment with the deferred intervention group and invited back to attend the PEP intervention as part of that group (see
Figure 1).

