### Data Analysis

First, descriptive statistics including mean, standard deviation, range, skewness, and kurtosis for all continuous variables as well as frequencies for all categorical variables will be calculated at each time point (T0-T4). Because of concerns about the relatively small sample size and low literacy/health literacy, the normality of all continuous variables will be assessed both graphically with histograms as well as statistically using the Shapiro-Wilk and Kolmogorov-Smirnov tests, and transformations will be made if necessary. Then we will assess for any baseline (T0) differences between two separate groups: (1) the randomly determined immediate intervention and deferred intervention groups and (2) all participants who attended the PEP intervention and those who did not. Both of these analyses will be conducted using chi-square test for categorical variables and either independent samples
*t*test or Wilcoxon rank sum test for continuous variables.

Next, analyses will be conducted within each intervention group to evaluate for any effect of the PEP intervention on the primary, secondary, and exploratory outcomes using chi-square test for categorical variables (eg, PAM level, PCS) and either repeated-measures
*t*test or Wilcoxon signed rank test for continuous variables (eg, PAM score, AURA, Krantz, SF-12v2 Health Survey, DSMQ, and HbA
_1c_). Initial assessment (T0) will be compared with each of the post-PEP assessments (T2-T4) for each variable. For the deferred intervention group, initial assessment (T0) will be compared with the assessment at the end of the waiting period (T1), which will then be compared with each post-PEP assessment (T2-T4).

After analyzing each group individually, the groups will be combined in order to have a larger sample size for pre- and post-PEP comparisons. Pre-PEP intervention data for these analyses will consist of data from enrollment (T0) for participants in the immediate intervention group and data collected at the end of the waiting period (T1) for participants in the deferred intervention group. Repeated-measures analyses will be conducted on the primary, secondary, and exploratory outcomes as described above and pre-PEP data (either T0 or T1) will be compared with each post-PEP assessment (T2-T3).

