Finally, multivariate analyses will be conducted using a series of generalized mixed-effects models to determine what effect patient characteristics, group membership, and time have on each continuous outcome measure. In each model, the dependent variable will be the outcome measure (eg, PAM, AURA, Krantz, SF-12v2 Health Survey, DSMQ, and HbA
_1c_). Independent variables will include participant characteristics such as age, sex, race/ethnicity, education level, annual income, number of years with T2DM, and health literacy as measured by the NVS. Other independent variables will include group (immediate vs deferred intervention) and time (T0-T4).

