## Results

Recruitment for this study began in November 2014. As of June 2015, we met our enrollment goal of 80 patients. However, because of differences in site policies, the distribution of enrolled participants does not match our initial goals. By site, we have enrolled 40 participants from Bellevue Hospital Center, 31 from Gouverneur Health, and 9 from Woodhull Medical Center. As Woodhull Medical Center is located in a different part of New York City and serves a slightly different patient population, we plan to return to that site within the next few months to recruit an additional 11 patients.

Out of these 80 participants enrolled, the 71 from Bellevue Hospital Center and Gouverneur Health have been invited to attend the PEP intervention. Because of staff turnover and site-specific policies, we have as of yet been unable to hold any PEP intervention sessions at Woodhull Medical Center. Of the 71 participants invited to attend the PEP intervention, 45 have attended PEP session 1, 36 have attended the full PEP intervention, and 33 have returned for the post-PEP focus group. Of the 11 participants switched from the immediate intervention group to the deferred intervention group, 6 completed the T1 assessment and 3 attended at least one session of the PEP intervention. Coding and thematic analysis of the focus group discussions is not completed, but participants have reported that the PEP intervention was not only acceptable but a valuable experience that made them feel more empowered in their own health care. Several participants have even reported seeing their HCPs after completing the PEP intervention and changing their behaviors in the visit, which resulted in improvement in the quality of their visit.

Follow-up data collection is still underway and all patients who attended at least PEP session 1 will be called for all follow-up data points. Follow-up data collection is scheduled to conclude in April 2016 and the results of our data analysis are expected to be available by June 2016.

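### Visit-by-visit paired tests estimate the pre/post-PEP change only in participants with both values, and the all-data mixed model already planned is not made the source of that estimate

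*Protocol article*

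**What the plan says.** Under Data Analysis, the within-group evaluation of PEP uses "either repeated-measures *t*test or Wilcoxon signed rank test for continuous variables", with PAM score, the primary outcome, among the variables listed. The initial assessment "will be compared with each of the post-PEP assessments (T2-T4) for each variable". For the deferred group, the end-of-wait assessment (T1) is also compared with each of T2 to T4.

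The groups are then combined for a larger sample. The pre-PEP value is T0 for the immediate group and T1 for the deferred group, and "Repeated-measures analyses will be conducted on the primary, secondary, and exploratory outcomes as described above and pre-PEP data (either T0 or T1) will be compared". The comparators are the post-PEP assessments, here written T2-T3.

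The section ends with a model-based step for the continuous outcomes: "multivariate analyses will be conducted using a series of generalized mixed-effects models to determine what effect patient characteristics, group membership, and time have on each" of them. The listed terms are participant characteristics, group and time (T0-T4). No interaction is named, and no analysis is designated as primary.

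Two other places bear on loss. The Sample Size section explains over-enrolment with "In anticipation of significant participant dropout over the course of the study". The Results section reports that "45 have attended PEP session 1, 36 have attended the full PEP intervention, and 33 have returned for the post-PEP focus group", and that everyone who attended at least session 1 will be called for all follow-ups.

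**The concern.** The objective is to "determine if a PEP will change patient preference for control in medical decision making, improve patient self-efficacy in patient-HCP communication, and increase patient activation". A paired test answers this only for people measured on both occasions. Someone with pre-PEP and T2 scores but no T3 is absent from the T3 test, and the T2 score is not used to inform the missing T3. A deferred participant without T1 has no pre-PEP value as the article defines it, and so leaves every pooled test. The results at successive visits may therefore describe different subsets.

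This is harmless if loss is unrelated to response. That is not a safe assumption here, because activation and willingness to keep answering follow-up calls may well be linked. If they are, an apparently sustained change at a later visit could partly reflect who is still responding. The pooled comparison is the plan's largest-sample look at PEP, so its estimate matters most.

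**Working it through.** **1. The stated sample size belongs to the paired test.** Inputs from Sample Size: d = 0.48, alpha 0.05 (taken as two-sided), power 0.80.

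- Normal formula: n = ((1.960 + 0.842)/0.48)² = 34.07, so 35.
- Exact paired t test: 37 (power 0.811); n = 36 gives power 0.7996.
- Two independent means would need 69 per arm.

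The stated n = 36 therefore fits a two-sided paired pre/post comparison.

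**2. What is known about loss.** Of 45 at session 1, 9 (20%) did not attend the full PEP and 12 (27%) did not return for the focus group. These are attendance figures, not missing outcomes: Follow-Up allows T2 by telephone and plans T3 and T4 by telephone. I use 20-27% only as an assumed range for T3 loss.

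**3. Bias of the complete-pair estimate at T3.** Assumptions, none from the article: n = 45; standardised T2 and T3 changes bivariate normal with SD 1 and correlation 0.5 or 0.7; T2 known for all; log-odds of T3 loss falling by 0.5 or 1.0 per SD of T2 change; 5,000 simulated trials per setting. Bias in SD of change:

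| Loss | Correlation | Slope 0.5 | Slope 1.0 |
|---|---|---|---|
| 20% | 0.5 | +0.053 | +0.090 |
| 20% | 0.7 | +0.069 | +0.121 |
| 27% | 0.5 | +0.061 | +0.112 |
| 27% | 0.7 | +0.091 | +0.161 |

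Relative to the planned effect: 0.053/0.48 = 11% and 0.161/0.48 = 34%. With no true effect, the nominal 5% test rejects in about 6-14% of trials. The likelihood estimate (T3 change regressed on T2 change, then averaged over all 45) is within 0.005 SD of the truth. With loss unrelated to response neither estimate is biased. The SD of the estimate then falls from 0.168 to 0.164 (20% loss, correlation 0.5) or from 0.175 to 0.164 (27%, 0.7), that is by about 2-6%.

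**4. Where the likelihood model helps less.**

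- T2 also missing for those who miss T3: same bias as the paired estimate, 0.05-0.17 SD. T2 missing for half of them: 0.02-0.07 SD.
- Loss depending on unseen values. Separate simulation on the PAM scale for T4 (assumed SD 12.5, correlation 0.5 or 0.7, true change 6 points, about 27% lost after T2):

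| Loss mechanism | Paired | All-data likelihood |
|---|---|---|
| Completely at random | 6.0-6.1 | 6.1 |
| On observed T2 change | 7.3-7.5 | 5.9-6.1 |
| On unseen T4 change | 8.5-9.2 | 7.2-7.6 |

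- Outcomes not measured at T2. Table 1 shows no T2 for DSMQ, SF-12v2 or HbA1c, so there is no early response to borrow from when T3 is missing.

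**5. The direction can reverse.** If low baseline activation drives loss (27%, pre/post correlation 0.5-0.7, slope 0.5-1.0), complete-pair change is understated by 0.05-0.11 SD, because those who remain start higher and regress toward the mean.

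**6. What the planned mixed model gives as listed.** With group and time as main effects only, a T3-minus-T0 contrast includes, for deferred participants, any change during the wait. That is not the pre/post comparison the article defines, which uses T1 for that group.

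**The case against.** The strongest reply is that the plan already contains an all-available-data model for the same outcomes. Fitted in the usual way it keeps people with incomplete follow-up, and if time is categorical, T1 is its own level and can serve as a reference. Which contrasts are reported could be left to an analysis plan. Part of this stands: the plan does not ignore incomplete data, and what remains is which analysis supplies the PEP effect. But the article does fix the paired tests as the pre/post evaluation, sizes the study on one, and gives the models another stated purpose.

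Three stronger readings are tempting and not supported.

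- *The PEP effect will be overstated.* The documents hold no outcome data on who leaves, and the direction depends on that.
- *Follow-up loss of 20-27% has been observed, or was foreseen.* The counts are session and focus-group attendance. The anticipated dropout explains enrolling 80 so that 40 complete PEP; it sets no expectation for loss afterwards.
- *A mixed model removes the problem.* It does so only with T2 observed and loss depending on observed values.

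A further fair objection is that merging T0 and the deferred group's T1 into one untreated occasion would assume no change over a 3-4 month wait that the design sets out to measure, and during which diabetes handouts were mailed. The model should keep them apart.

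**Conclusion.** The point holds in a limited form. The paired tests give the change among those with both values at each visit, which is a biased estimate for all attenders if loss after PEP is related to response. Under the assumed 20-27% loss driven by observed T2 change, the PAM estimate at T3 is about 0.05-0.16 SD too high, or 11-34% of the planned effect. With loss unrelated to response there is no bias, only a small loss of precision. A likelihood model is no worse in bias in the settings examined and clearly better when T2 is observed. It does not protect against loss on unseen values, and offers less for DSMQ, SF-12v2 and HbA1c. Since the plan already intends such models, making them the main source of the PEP estimate is worth doing before analysis.

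**What to change.** Take the main pre/post-PEP estimates for the continuous outcomes from the mixed model already planned, specified as follows:

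- Fit by likelihood to all available assessments of everyone who attended at least session 1.
- Treat T0, T1, T2, T3 and T4 as separate categorical occasions (where measured), with group-by-time terms, within-person correlation and a small-sample degrees-of-freedom correction.
- Define the pre-PEP reference as T0 for the immediate group and T1 for the deferred group, without merging T0 and T1. Deferred participants lacking T1 still contribute their other assessments.
- Report a contrast from the reference to each post-PEP visit, and reconcile the pooled range (T2-T3) with the within-group range (T2-T4).
- Keep the paired tests as a sensitivity analysis, with the number of pairs at each visit, and add a sensitivity analysis for non-random loss.

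The cost is plan wording and modest programming, with no new data, visits or participants; follow-up was still under way when the article was written. The downside is reliance on missing-at-random and covariance assumptions in a small sample.

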## Methods

### Overview

The PEP is a randomized, wait-list control study (see
Multimedia Appendix 1) that aims to enhance general communication skills so that patients can participate in SDM during office visits, become activated in their own health care, and better manage their medical conditions.

Patients were recruited in cohorts of 20 and then randomly assigned to attend the PEP intervention immediately (immediate intervention) or after a waiting period (deferred intervention). All participants completed a baseline assessment at the time of enrollment (T0) and will complete follow-up assessments 1 week (T2), 3 months (T3), and 6 months (T4) after completion of the PEP intervention (see
Figure 1). Additionally, the deferred intervention group was assessed at the end of the waiting period (T1), immediately before being invited to attend the PEP intervention. The T1 assessment for the deferred intervention group was approximately 3-4 months after randomization and was timed to coincide with the T3 assessment of the immediate intervention group. A wait-list control design was chosen to create a control group with multiple time points of data collection (deferred intervention T0-T1) while still allowing for all participants who enrolled in the study to complete the PEP intervention and post-PEP follow-ups.

Aside from attending the PEP intervention, all participants continued to receive their usual care, including all scheduled primary care and specialty clinic appointments, HbA
_1c_monitoring, and all medications as directed by their physicians.

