### Recruitment, Randomization, and Retention

Research assistants (RAs) screened all of the clinic appointments each day to identify patients who were eligible for the study. Research assistants then briefly explained the study to all eligible patients who came to their appointment and obtained informed consent from those who decided to enroll (see
Figure 1). After obtaining informed consent, RAs read participants a set of questionnaires to complete the initial (T0) assessment (see
Table 1).

After 20 participants were enrolled in the study, a Web-based random number generator was used to generate a list of 20 integers between one and two. The list was refreshed until it contained 10 ones and 10 twos. Based on this list, participants were assigned in order of their study identification number to the immediate intervention (1) or deferred intervention (2) group. All participants in the immediate intervention group were contacted by phone to schedule the PEP intervention sessions and all participants in the deferred intervention group were contacted by phone and informed that they would be recontacted in 3-4 months to schedule their PEP intervention sessions.

Participants were compensated for participating in the study. They received US $10 and a MetroCard with US $10 at each of the two PEP intervention sessions. They also received US $60 and a MetroCard with US $10 for completing the study if they attended a post-PEP focus group.

In order to increase retention of deferred intervention participants, they received a letter from our program and an educational handout about T2DM in the mail approximately every 3 weeks. Handouts were sent in the same order and all handouts came from the Diabetes Care and Education website [
50]. In total there were four mailings: (1) Nutrition to Help Manage your Diabetes and Weight, (2) Eating Healthy on a Lean Budget, (3) Know Your Blood Sugar Numbers, and (4) Managing and Preventing Hypoglycemia. All four of these handouts were short, only 1-2 pages in length, and contained general information about T2DM that participants should have already obtained from their HCPs as part of their routine treatment. Therefore, we do not expect that receiving these handouts will cause a significant difference in the two randomized groups or otherwise affect the results of the study.

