### Outcome Measures

Outcome measures for the study primarily consist of self-report questionnaires assessing health attitudes and behaviors (see
Table 1). Because of the low literacy of the patient population, RAs read all questionnaires to the participants and then recorded their responses. All questionnaires were asked in the same order and a standardized protocol was created so that all RAs asked and clarified questions in the same manner. Outcome measures were assessed at the time of enrollment (T0), after the waiting period (T1: deferred intervention group only), and postintervention after 1 week (T2), 3 months (T3), and 6 months (T4).

**Table 1 table1:** Data collection.

Domain	Measures	Timing of assessment			
		Enrollment (T0)	After waiting period (T1) ( *deferred only*)	1 week after PEP ^a^ (T2)	3 and 6 months after PEP (T3, T4)
Demographics	Age, sex Race and ethnicity Education level Annual income	X			
Clinical characteristics	Number of years with diabetes Current diabetes treatment	X			
Health literacy	Newest Vital Sign [ 51- 53]	X			
Patient activation	Patient Activation Measure [ 23]	X	X	X	X
Ability to obtain information from HCPs ^a^	Ask, Understand, Remember Assessment [ 54]	X	X	X	X
Preference for control in medical decision making	Krantz Health Opinion Survey [ 55]	X	X	X	X
	Preference Control Scale [ 56]	X	X	X	X
Disease management	Diabetes Self-Management Questionnaire [ 57]	X	X		X
Health quality of life	SF-12v2 Health Survey [ 58]	X	X		X
Biological marker of disease severity	Hemoglobin A _1c_	X	X		X
PEP intervention feedback	Qualitative data analysis of focus group discussion			X	

^a^PEP: Patient Empowerment Program; HCP: health care provider.

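### The mixed model's group term compares the arms only at visits where both have the same PEP status, and no planned analysis makes the concurrent randomised contrast

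*Protocol article*

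**What the plan says.** The last step of the Data Analysis section is a series of mixed models "to determine what effect patient characteristics, group membership, and time have on each continuous outcome measure". After the patient characteristics it adds: "Other independent variables will include group (immediate vs deferred intervention) and time (T0-T4". It names no group-by-time term, no indicator of having received PEP and no time since randomisation.

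The visit labels are defined elsewhere. Under Overview, participants "will complete follow-up assessments 1 week (T2), 3 months (T3), and 6 months (T4) after completion of the PEP intervention", so T2 to T4 run from the end of the intervention, not from randomisation. Under Outcome Measures, one assessment is made "after the waiting period (T1: deferred intervention group only". Overview also aligns this assessment with T3 in the other arm: "The T1 assessment for the deferred intervention group was approximately 3-4 months after randomization and was timed to coincide with the T3 assessment".

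The other outcome analyses are paired pre-post tests, first within each group and then with the groups pooled. The deferred group's T0 is also compared with its T1.

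**The concern.** A wait-list design identifies the intervention effect in the window when one arm has had the intervention and the other has not. Here that is 3-4 months after randomisation: immediate T3 against deferred T1. In the model these two assessments carry different labels, so each is absorbed by its own time effect. What is left for the group coefficient is the difference between arms at labels where their PEP status is the same.

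Two things follow. The only outcome analysis that contains group as a term cannot show whether PEP works. And because the deferred group reaches T2-T4 some 3-4 months later than the immediate group, any general change over time shows up as a group difference. As planned, the primary outcome (PAM) never receives a concurrent randomised comparison.

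**Working it through.** **PEP status at each label**

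| Label | Immediate | Deferred | Same status? |
|---|---|---|---|
| T0 | before PEP | before PEP | yes |
| T1 | not assessed | before PEP | no comparison |
| T2, T3, T4 | after PEP | after PEP, about 3.5 months later | yes |

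**Inputs**
- From the article: 1:1 allocation ("The list was refreshed until it contained 10 ones and 10 twos"); an offset of 3-4 months (3.5 used); PAM gains of 4-8 points and d = 0.48 (Sample Size); 80 enrolled, a target of 40 completers, and 45 attending session 1 (Sample Size, Results).
- Assumed: SD = 6/0.48 = 12.5 from the midpoint gain (range 4/0.48 = 8.3 to 8/0.48 = 16.7); ICC 0.5-0.7; linear drift of 0-2 PAM points per month; the same PEP effect in both arms; two-sided alpha. The article gives no SD, ICC or drift.

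**The plan's own figure.** The stated n = 36 is a pre-post figure. A paired t-test at d = 0.48, two-sided alpha .05 and power .80 needs 37 by the noncentral t (power at 36 is 79.96%) and 35 by the normal approximation, so 36 is reproduced. A two-arm comparison at d = 0.48 would need 69 per arm.

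**Expected group coefficient, categorical time.** T1 has its own parameter and only one arm, so it drops out. The coefficient is the mean immediate-minus-deferred difference over T0, T2, T3 and T4.
- No drift: (0 + 0 + 0 + 0)/4 = 0 for a PEP effect of 0, 6, 12 or 25 points. The rejection rate is 5%.
- Drift of b points per month: (0 - 3.5b - 3.5b - 3.5b)/4 = -0.75 × 3.5 × b. This is -1.3 at b = 0.5, -2.6 at b = 1 and -5.3 at b = 2, whatever PEP does.

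If time enters as a linear label score, a 6-point PEP effect gives a group coefficient of 0.48 (rejection 5-6%), and drift of 1 point per month with no PEP effect gives -2.8. The conclusion is the same.

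**Rejection rates with no PEP effect, full follow-up.** SE = SD × √[(ICC + (1 - ICC)/4) × 2/n]. At n = 40 per group this is 2.21 (ICC 0.5) to 2.46 (ICC 0.7). At n = 20 and ICC 0.7 it is 3.48.

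| Drift per month | 20 per group | 40 per group |
|---|---|---|
| 0.5 | about 7% | 8-9% |
| 1 | 12-13% | 19-22% |
| 2 | 33-39% | 57-66% |

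**Incomplete attendance.** With 45/80 = 56% contributing post-PEP data (REML simulation, 40 per group enrolled, ICC 0.6, 300 runs), drift of 1 point per month gives a mean coefficient of -1.6 and 7% rejection. Drift of 2 gives -3.5 and 28%. A 6-point PEP effect without drift gives -0.17 and 4%.

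**Where the PEP effect goes.** With PEP = 6 and no drift, the T2, T3 and T4 coefficients are 6, 6 and 6. With PEP = 0 and drift of 1 point per month they are 2, 5 and 8. The time coefficients alone cannot tell benefit from drift.

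**The concurrent contrast.** Immediate (T3 - T0) minus deferred (T1 - T0) has SE = SD × √[2(1 - ICC)] × √(2/n). This is 3.95 (ICC 0.5) to 3.06 (ICC 0.7) at 20 per group, and 2.80 to 2.17 at 40 per group.
- It recovers 6.0 with no drift and 5.75 with drift of 1 point per month.
- With no PEP effect and that drift it gives -0.25 and about 5% rejection.
- Power for 6 points is 33-50% at 20 per group and 57-79% at 40 per group. Baseline adjustment multiplies the variance by (1 + ICC)/2, that is 0.75 to 0.85, so power would be somewhat higher.

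**The case against.** **The group coefficient is not named as the test of PEP.** This stands. A reader might infer that the plan will judge PEP by this coefficient and read a null result as no effect. The article does not say so: it gives the evaluation of PEP to the pre-post tests and sizes the trial for them. A reader might also infer that this is the only analysis containing both groups. It is not, because the pooled pre-post analysis and the baseline comparison contain both. The supportable statement is that no other planned outcome analysis has group as a term and none compares treated with untreated participants at the same time.

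**The listed terms may not be the whole model.** The text says the variables will include group and time, the article is condensed, and an interaction is not ruled out. That is fair, but an interaction on these labels would still compare post-PEP with post-PEP at T2-T4. The fault lies in the stated time coding, not in detail left unsaid.

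**Deferred T0 versus T1 is a safeguard.** It is, in part. It shows change during the wait, but it is a within-group test and is not set against the immediate group's change.

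**The drift is assumed.** This stands. A reader might take a false-positive rate near 20% as expected. It needs drift of 1 point per month and 40 per group with full follow-up. The article reports no drift and expects no meaningful effect from the mailed handouts. At 0.5 point per month, or at 56% attendance with 1 point per month, the inflation is small.

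**The proposed contrast has its own limits.** This also stands. Results says follow-up calls go to those who attended at least session 1, so immediate T3 comes from attenders, while deferred T1 precedes the invitation. Eleven immediate participants were moved to the deferred group, of whom 6 completed T1.

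**Site and cohort.** Patients were allocated in blocks ("After 20 participants were enrolled in the study, a Web-based random number generator was used to generate a list of 20 integers"), and one site "serves a slightly different patient population". A reader might count the absence of site and cohort from the model as part of the error. It is not: leaving them out does not bias a 1:1 randomised contrast, and adding them is a choice about efficiency.

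**Conclusion.** The concern holds. With group and visit label as the stated terms, the group coefficient cannot show the PEP effect: it is about zero if PEP works similarly in both arms. This half needs no assumption about SD, ICC or sample size, and with linear label time it is near zero rather than exactly zero. Drift shifts the coefficient by about -2.6 points for each 1 point per month. That half depends on a drift the article does not report, so its practical size ranges from negligible to substantial. PEP-related change remains visible in the time coefficients and the pre-post tests, but there it can be separated from drift only in part, through deferred T0-T1. The contrast that uses the randomisation, for which the article deliberately aligns deferred T1 with immediate T3, appears in no planned analysis.

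**What to change.** 1. Code assessments by time since randomisation, so that immediate T3 and deferred T1 share one 3-4 month visit, and include group by visit. Alternatively, replace group by a time-varying indicator of having received PEP, together with calendar time. That version follows receipt of PEP rather than allocation.
2. State that the between-group PEP effect is the baseline-adjusted difference between immediate T3 and deferred T1, by original randomised group, and report it with its confidence interval.
3. Keep the 11 switched participants in the immediate arm and use their T1 assessment, where completed, as their 3-4 month value.
4. State that T3 follow-up of attenders only limits this contrast, because the immediate arm is then more selected than the deferred arm.
5. Do not present the coefficient for group from a model on the T0-T4 labels as evidence for or against PEP.
6. Optionally add site or randomisation cohort for precision.

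The assessments are already scheduled, so the cost is analysis wording and work. The price is modest power (figures above), so the interval should carry the interpretation and a non-significant result should not be read as absence of effect.
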